### Data analyses

Data will be analysed using qualitative and statistical methods. All eligible participants will be included in the analysis. The statistical analyses will be performed with R. The categorical and numerical data will be analysed using one-way analysis of variance (ANOVA). Qualitative analysis will be presented thematically [42].

For the measurement data from the system:

Data pre-processing: Data will be investigated where water and soaping data are combined to single handwashing procedures. Data points that are not valid (outside of kindergarten opening hours) will be removed. The descriptive statistics of the clusters, randomization checks, ICC (intracluster correlation) will be calculated. The data will be analyzed using linear fixed-effect regression model for panel data, and dependent variable soaping time. The four groups will be compared in baseline, intervention, and post-intervention phases.

For the survey and staff interview data:

The comparison among the groups will be implemented using random effects regression, allowing for the clustered nature of the data, and adjusted using the covariates of the adjusted analyses (when a small number of clusters are present) [43]. Simple bias analysis will be used to quantify the uncertainty of the biases such as confounding variables [33]. The qualitative results of the survey and kindergarten staff interview will be analysed and compared thematically. The four groups will be compared after intervention phase.

For the children interview and observation data:

The analyses will be compared among groups based on the complete data only. The comparative analyses approach used to calculate the observation, survey, and staff interview will be used. The self-efficacy measurement scale will be developed and evaluated for its psychometric properties [44,45]. The qualitative result of the observation and interviews will be analysed and compared thematically [42]. Children who will participate the interview at one time point will be considered as missing data, these will be excluded from the analysis. The four groups will be compared in baseline, intervention, and post-intervention phases.

For the sickness day data:

The total sick leave days are compared among the groups one year before and after the start of the baseline phase.

The statisticians of the two universities will validate the statistical results of the data.

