### Sample size

The sample size is calculated based on the significant effects found during the pre-study. In the pre-study, 10,000 handwashing events were recorded over a period of 42 days in a treatment group (n = 82 children in two clusters) and a control group (n = 53 children in two clusters). Using Cohen’s power analysis with f^2^ = 0,35 (large effect size) and power level of 0.8 and 2 predictors and a probability level of 0.05 leads to n = 31. However, since randomization is on a cluster level, the n must be increased. With the ICC from the pre-study of 0.062, and estimated cluster size (size of each kindergarten) of 40 children, we calculate the design effect:

D=1+(m−1)*ICC=1+(40−1)*0.062=3.418

Thus, we need to increase the sample size by 3.418 compared to individual randomization, due to cluster randomization leading to 106 participants (n = 31 * 4.418 = 106). With the assumption of a cluster size of 40 children per kindergarten, this leads to three kindergartens that need to participate in the study. Each kindergarten represents one cluster and gets assigned to be the control, the intervention A, B, and C groups. Two intervention groups will be covered by one cluster.

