### Randomization

The cluster randomization will be at the kindergarten level. Kindergartens will be randomly assigned to control or intervention groups by two researchers that are not members of the research team and are stratified by country. One kindergarten serves as one cluster. Simple randomization will be used which will be drawing lots, where each cluster will be assigned a number in a piece of paper. The parents will enrol their children for participation in the study within the time set through the website link provided and email.

No information will be given regarding the allocation. Allocation will be about four weeks before the start of the baseline phase and will be conducted by the two non-member researchers. They will generate the allocation sequence, enroll the participants, and assign them to control or intervention groups. There will be complete concealment of the allocation from the members of the research team and the participants, to exclude the possibility of predicting the next allocation [33].

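### The general one-way ANOVA rule ignores the randomised kindergarten and contradicts the random-effects models in the same section, and the primary sensor model states no allowance for clustering in its inference

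*Protocol article*

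**What the plan says.** All references are to the protocol article.

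- **Randomization.** Whole kindergartens are allocated by drawing lots, and they "are stratified by country".
- **Sample size.** The individual-level figure comes from "power level of 0.8 and 2 predictors and a probability level of 0.05 leads to n = 31". It is then inflated for clustering: "With the ICC from the pre-study of 0.062" and an expected 40 children per kindergarten. The result is 106 children in three kindergartens, with two of the intervention groups placed in one of them.
- **Data analyses, general rule.** "The categorical and numerical data will be analysed using one-way analysis of variance (ANOVA". No outcome is exempted.
- **Data analyses, sensor data (the primary outcome).** "The data will be analyzed using linear fixed-effect regression model for panel data, and dependent variable soaping time". The section also promises cluster descriptives, randomisation checks and an ICC, and a comparison of the four groups in each of the three phases, baseline included.
- **Data analyses, survey and staff interviews.** Random-effects regression "allowing for the clustered nature of the data". The child interview and observation paragraph carries this approach over.
- **Data analyses, sick leave.** Totals are compared between groups. No method is named beyond the general rule.

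**The concern.** The trial is sized for clustering, yet the general test treats children as independent. One-way ANOVA also has no term for the repeated measurement of the same kindergartens over three phases, and it is not a method for categorical responses such as single three-point items. A reader cannot tell whether the ANOVA or the random-effects regression governs the child, parent and staff outcomes. For sick leave the ANOVA is the only method on offer.

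The primary outcome has the least explicit protection. The sensor paragraph does not say what the fixed effects are (kindergarten, sink or time), at what level the panel is formed, or how standard errors are obtained. An ICC will be calculated, but no use of it in inference is stated. Sensor data are numerous, so if single handwashing events were treated as independent, standard errors would be small compared with the variation between kindergartens and phases. At stake is whether a significant difference between arms can be told from an ordinary difference between kindergartens.

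**Working it through.** **1. The plan's own figure.** Multiple regression with f² = 0.35, 2 predictors and alpha 0.05; noncentral F with 2 and n − 3 df and noncentrality 0.35n. At n = 31 the power is 0.804, so 31 is reproduced. Design effect: 1 + 39 × 0.062 = 3.418, and 31 × 3.418 = 105.96, so 106. The multiplier 4.418 printed in the final product would give 136.96 and reads as a misprint.

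**2. One-way ANOVA that ignores kindergarten.** Take no true effect, normal outcomes, equal cluster sizes m and one kindergarten per arm. The ratio of expected between-group to within-group mean squares should be 1. It is

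1 + m × ICC / (1 − ICC) = 1 + 40 × 0.062 / 0.938 = 3.64.

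Simulated type I error at nominal 0.05 (200,000 replicates; the same code returns 0.050 at ICC 0):

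| Setting | ICC | Type I error |
|---|---|---|
| 4 arms, 40 per kindergarten, 1 kindergarten per arm | 0.062 | 0.53 |
| 4 arms, 40 per kindergarten, 2 to 10 kindergartens per arm | 0.062 | 0.52 |
| 3 groups of 35 (106 / 3) | 0.062 | 0.40 |
| A pair of arms, 40 each | 0.062 | 0.30 |
| 4 arms, 10 per kindergarten, 1 or 2 kindergartens per arm | 0.062 | 0.18, 0.17 |
| 4 arms, 40 per kindergarten, 1 per arm | 0.01 to 0.10 | 0.13 to 0.69 |

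More kindergartens do not cure the test, because it still does not use them as the unit.

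**3. Sensor model, reading A: kindergarten or sink fixed effects.** Rank of the design matrix, four arms and three phases:

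| Kindergartens per arm | Kindergarten + phase | + arm | + arm-by-phase | Cells |
|---|---|---|---|---|
| 1 | 6 | 6 | 12 | 12 |
| 2 | 10 | 10 | 16 | 24 |

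Arm adds no rank, so baseline arm differences are not estimable. Changes from baseline are. The exception under kindergarten effects is the contrast between the two arms that share a kindergarten; sink effects would absorb that too if each sink stays in one arm.

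For the size of the error, the pre-study gives 10,000 events / 4 clusters / 42 days × 21 days = 1,250 events per kindergarten and phase. Let r be the correlation of kindergarten means between phases, an assumption because the protocol gives none. With unclustered errors, the variance of a two-arm change contrast is understated by the factor

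1 + 1,250 × 0.062 × (1 − r) / 0.938,

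and type I error is 2 × [1 − Φ(1.96 / √factor)].

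| r (assumed) | Factor | Type I error |
|---|---|---|
| 1.0 | 1.00 | 0.05 |
| 0.95 | 5.13 | 0.39 |
| 0.9 | 9.26 | 0.52 |
| 0.8 | 17.52 | 0.64 |

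**4. Sensor model, reading B: time effects only.** Baseline arm differences can be estimated, but clustering is ignored. A four-arm event-level ANOVA with 1,250 events per kindergarten, used as a guide, rejects in 0.99 of trials if 0.062 applies to events, and in 0.78 at ICC 0.005.

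**5. Can the analysis alone repair this?** A test on kindergarten values for four arms with c kindergartens each has 4(c − 1) error df: 0 for c = 1 and 4 for c = 2. Three kindergartens for four arms leave none. Permutation within country has at most two arrangements if three kindergartens split two and one, so p cannot fall below 0.5. A random kindergarten effect cannot separate arm from kindergarten either.

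**The case against.** The best defence is that the ANOVA sentence is a loose introduction and the specific paragraphs override it. Those paragraphs plan random effects for clustering, with covariate adjustment for few clusters, and extend this to child interviews and observations. It would therefore be wrong to infer that clustering is handled only for the survey. This stands: the inflation in step 2 reaches those outcomes only if the general sentence governs. But nothing in the text says that it does not, and sick leave has no other method.

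For the sensor model the defence is stronger. Kindergarten effects would remove stable differences between kindergartens, aggregation to a sink-day panel is not excluded, and standard-error methods are often left to a statistical analysis plan. A reader might infer that the model both ignores the randomised unit and cannot make the baseline comparison. Those two complaints largely belong to different readings (B and A), and the protocol does not say which applies. The baseline comparison may also be meant for the planned descriptives and randomisation checks.

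Finally, a cluster-level test cannot rescue a design with three kindergartens for four arms. That also stands, and it limits what the fix can promise.

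**Conclusion.** The ANOVA sentence is wrong for this design as written and contradicts the models below it. If it governed, the four-arm type I error would be about 0.53 at the protocol's own ICC and cluster size, roughly ten times nominal. This assumes normal outcomes, equal cluster sizes and an ICC of 0.062 at child level; the protocol does not state the level.

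The sensor model is a narrower matter. It states no allowance for clustering in its inference, and each natural reading needs repair. The size of the error is conditional: 0.05 to about 0.64 under reading A, resting on unclustered errors, event-level data and an assumed r. A reader might infer that the primary result would probably be significant whether or not the display works. The documents do not support that, because r is given nowhere and the error is nominal at r = 1.

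A reader might also expect a gain in precision from pooling B and C during the intervention phase, when they are identical. That presumes separate kindergartens, whereas two intervention groups are to share one.

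**What to change.** - Delete the ANOVA sentence, so that the random-effects models govern child, parent and staff outcomes, and name a cluster-aware method for sick leave.
- For the sensor outcome, specify kindergarten effects with arm-by-phase contrasts (changes from baseline). Take uncertainty from kindergarten-by-phase variation, not from single handwashing events. Account for country, the randomisation stratum, where the number of kindergartens allows.
- Make the baseline comparison of arms descriptive.
- State that three kindergartens for four arms, two of them sharing one, leave no between-kindergarten error df. Report arm contrasts as exploratory estimates without confirmatory p-values unless there are at least two kindergartens per arm.

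The cost is analysis wording, a little programming, wider intervals and a more modest conclusion. Confirmatory tests would cost more, because they need additional kindergartens.

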### Hypotheses

Main effects: Control, Intervention A (instruction), Intervention B (instruction plus reward), and Intervention C (instruction plus reward and instruction in post-intervention phase) groups

H1: Feedback display will increase handwashing activity in the kindergarten (in the short term) during intervention phase
For intervention A, B, and C groupsFor intervention B and C groups more than intervention A groupH2: Handwashing activity in the kindergartens will decline with time (while the display will still be turned on)
For intervention A group less than intervention B and C groups during the beginning of the post-intervention phaseFor intervention B group less than intervention C group during post-intervention phase.For control group less than intervention A, B, and C groups in all phases.Motivation crowding out: Measurement-basedH3a: Effect will partially persist, when feedback display in kindergarten will be turned off during the beginning of post-intervention phase. For intervention C groups less than intervention A and B groups. (Explanation: habit will be formed, there will be partial motivation crowding out, impact in increased self-efficacy will be stronger)H3b: Effect will vanish and handwashing will return to baseline behaviour for intervention B group in post-intervention phase. (Possible explanation: no habit will be formed, there will be no motivation crowding out)H3c: Effect will vanish and handwashing activity will drop below baseline behaviour for intervention A group in post-intervention phase. (Possible explanation: there will be crowding out)
Acquisition of competences and self-efficacy: Intervention A, B, and C groupsH4a: Feedback intervention will increase competences and self-efficacy level of children after the intervention phase–for intervention B and C groups stronger than for intervention A groupH4b: Feedback intervention will increase competences and self-efficacy level of children after post-intervention phase–for intervention C group stronger than for intervention B group and for intervention B group stronger than for intervention A group.

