### Data collection

This study will start in mid-year of 2022 and will last for a year. The data will be analysed using quantitative and qualitative methods. The child’s age and gender will be collected. The implementation phases and timeline of the data collection are shown in Figs 1 and 2.

The handwashing activity data from the system will be recorded every day during the baseline, intervention, and post-intervention phases. The parent survey data will be given and collected within the last week of the intervention phase. The kindergarten staff interview data will be collected during the last week of the intervention phase and right in the beginning week of the post-intervention phase to evaluate the observed effect of children’s hand hygiene behaviour and reactions towards the removal of the instructions and reward. The children’s observation sessions and interviews will be collected during the last weeks of the baseline, intervention, and post-intervention phases. The number of sick leave days will be collected from the sick leave records provided by the kindergarten staff one year before and after the start of the baseline phase.

The follow-up strategy will include sending updates of the study phases through email to the kindergarten managers and staff. The email includes the details of reminding how and when the participants will be contacted for follow-up. It will also include updates on the contact information of the participants.

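### H4a and H4b claim an increase and an ordering of arms in children's self-efficacy, but the planned comparison names no contrast that uses the baseline interview and observation

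*Protocol article*

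**What the plan says.** All references are to the protocol article.

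- **Hypotheses.** H4a: "Feedback intervention will increase competences and self-efficacy level of children after the intervention phase", more strongly in B and C than in A. H4b: "Feedback intervention will increase competences and self-efficacy level of children after post-intervention phase", with C ahead of B and B ahead of A.
- **Data collection.** "The children’s observation sessions and interviews will be collected during the last weeks of the baseline, intervention, and post-intervention phases". The child measures therefore have one value before the intervention and two after it starts. The parent survey is taken only in the last intervention week. The staff interview is taken in that week and in the first post-intervention week. Neither has a pre-intervention value.
- **Data analyses, general rule.** "The categorical and numerical data will be analysed using one-way analysis of variance (ANOVA".
- **Data analyses, survey and staff interview.** "The comparison among the groups will be implemented using random effects regression, allowing for the clustered nature of the data, and adjusted using the covariates". These come from adjusted analyses that are not listed.
- **Data analyses, child interview and observation.** "The comparative analyses approach used to calculate the observation, survey, and staff interview will be used", so the random effects regression carries over. Then: "Children who will participate the interview at one time point will be considered as missing data, these will be excluded from the analysis". The paragraph ends: "The four groups will be compared in baseline, intervention, and post-intervention phases".
- **Sample size.** Three kindergartens are planned for four arms, with two intervention groups in one kindergarten.

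**The concern.** H4a and H4b make two claims: that scores rise, and that they rise more in some arms than in others. Both concern change. A one-way ANOVA within a phase has one factor and no baseline or time term, and its null is that the four group means are equal in that phase. The regression carried over was written for sources that have no pre-intervention value, so nothing in it points to using one.

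In a trial with many clusters per arm, randomisation would make post-phase means a fair, if less precise, basis for comparison. Here there is about one kindergarten per arm, so chance differences between kindergartens pass straight into the comparison of arms. The baseline is the main means of removing their stable part.

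The overall test raises a second problem. It can reject because A, B and C all exceed control by the same amount. That would support an increase but contradict the ordering.

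At stake is how the self-efficacy and competence results are read. A significant phase-wise result could not by itself be taken as the increase or the ordering that H4 predicts.

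**Working it through.** **The plan's own figure.** Design effect = 1 + (40 − 1) × 0.062 = 3.418, and 31 × 3.418 = 105.96, which gives the stated 106. (The multiplier printed beside it, 4.418, would give 136.96. It looks like a slip and plays no part below.) The plan states no power or sample size for H4.

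**Inputs for the illustration.**
- From Sample size: total 106, four arms, ICC 0.062.
- Assumed: this ICC, which comes from the pre-study, applies to the child scales; each arm is one independent kindergarten of m = 106/4 = 26.5 children; the test is a child-level ANOVA that ignores clustering; there is no intervention effect.
- Also assumed: c, the correlation of a kindergarten's effect between phases, and r, the within-kindergarten correlation of a child's scores between phases. The article gives neither.

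**Size of pre-existing differences.** The SD of the difference between two kindergartens is √(2 × 0.062) = 0.35 outcome SDs.

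**Levels in one phase.** The between-arm mean square is inflated by 1 + m × ICC/(1 − ICC) = 1 + 26.5 × 0.062/0.938 = 2.75. The 5% critical value of F(3, 102) is 2.694. The false-positive rate is P(F > 2.694/2.75) = 40.6%. Simulation with 5,000 runs per scenario gave 41%. With 40 children per arm the inflation is 3.64 and the rate about 54%.

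**Change from baseline.** The inflation is 1 + m × ICC × (1 − c)/[(1 − ICC)(1 − r)].

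| c | r | Inflation | ANOVA on change rejects |
|---|---|---|---|
| 1 | any | 1.00 | 5% |
| 0.9 | 0.5 | 1.35 | 12% |
| 0.8 | 0.5 | 1.70 | 20% |
| 0.8 | 0.7 | 2.17 | 30% |
| 0.5 | 0.5 | 2.75 | 41% |
| 0.5 | 0.7 | 3.92 | 56% |

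The two inflation formulas are equal when (1 − c)/(1 − r) = 1. Raw change therefore has the lower false-positive rate only when c exceeds r.

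**Shared kindergarten.** For the contrast (B + C)/2 − A on levels, the kindergarten variance is 1.5 × ICC with independent kindergartens, 0.5 × ICC if A shares with B or C, and 2 × ICC if B and C share. Keeping 26.5 children per arm, the inflations are 2.75, 1.58 and 3.34, and the false-positive rates about 23%, 12% and 28%. The sharing pattern changes the size of the problem.

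**The case against.** The strongest reply is that the article does not exclude use of the baseline. The sentence about comparing the four groups in three phases also closes the paragraph on the system data, which are analysed with a panel regression, so it may merely list the measurement occasions. The carried-over regression allows for clustering and adjusts for covariates that could include baseline. Excluding children seen at one time point makes most sense if each child's records are linked over time. Covariate lists and named contrasts are often left to an analysis plan. Comparison among groups can include pairwise contrasts, and a rejection when A, B and C all exceed control partly agrees with H4a, which also claims an increase.

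Much of this stands. A reader might infer that the plan tests pre-existing differences instead of change, or that it rules the baseline out. The text supports neither: baseline use is unstated, and a randomised post-phase contrast contains the intervention effect plus chance kindergarten differences, which the baseline comparison would help to reveal. A reader might also take 41% as this trial's error rate. It is not. The rate arises because a child-level test ignores clustering with one kindergarten per arm; with an ICC of zero, the level test holds its 5%. Nor is 5% assured for change.

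The reply does not remove the mismatch. The article goes beyond silence: it names a one-factor test and a phase-wise comparison for hypotheses about change. The regression it borrows comes from sources without a baseline. With about one kindergarten per arm, a random kindergarten effect cannot be separated from arm, so allowing for clustering does not replace the baseline.

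**Conclusion.** The point holds as a mismatch between hypothesis and stated analysis, for the child interview and observation outcomes. H4a and H4b concern increase and ordering, the baseline is collected, and no stated contrast uses it.

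The illustrated gain, from about 41% false positives on levels to between 5% and 20% on change, depends on the assumed ICC, four independent kindergartens, a test that ignores clustering, kindergarten effects correlating at least 0.8 between phases, and a child correlation of 0.5. If the kindergarten correlation does not exceed the child correlation, raw change gives no gain. The direction of the argument is firmer than the figures. These are secondary outcomes, so the change is advisable and does not affect the primary analysis.

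**What to change.** For the child interview scales and the observation checklist:

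1. Replace the phase-wise comparison and the one-way ANOVA with a repeated-measures model that uses the baseline, through group-by-phase terms or with baseline as a covariate. Exempt these data from the general ANOVA sentence.
2. Name the H4 contrasts. For the ordering: B and C together minus A after the intervention phase; C minus B, and B minus A, after the post-intervention phase. For the claimed increase: each intervention arm against control at both times.
3. Treat group comparisons at baseline as descriptive.
4. State that this reduces but does not remove the confounding of arm with kindergarten, because kindergartens may also drift differently over time.

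The cost is wording only, since the baseline measurements are already planned. Raw change is noisier than the post-phase score when a child's scores correlate below 0.5 between phases; entering baseline as a covariate limits that loss.

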**Fig 1 pone.0280686.g001:**
[figure not shown]
Schedule of enrolment, intervention, and assessments.

This study will be a four-arm cluster randomized controlled trial study with three phases and a twelve-month follow-up by country stratification. This study will evaluate the effectiveness of the gamified live feedback intervention on children’s handwashing behaviour, self-efficacy, and motivation in three different phases: the baseline, intervention, and post-intervention phases. In Finland, there will be a twelve-month follow-up after the baseline phase. This study will consist of four groups, the control group, and three different intervention groups. All the groups will have automated monitoring systems installed before the start of the baseline phase and will be available in all phases. The system will be de-installed after the post-intervention phase.

During the baseline phase, all the groups will have no screen activity. During the intervention phase, the control group will have no screen activity. The intervention A group will have a screen display providing handwashing instructions but no reward, and the intervention B and C groups will receive handwashing instructions and rewards from the screen display. During the post-intervention phase, all the groups will have no screen activity except the intervention C group which will receive handwashing instructions but no reward (Fig 2).

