### Implementation

This study will be composed of three phases, the baseline, intervention, post-intervention, and a twelve-month follow-up (Fig 2). The first phase will be the baseline which will last for three weeks. The systems will be installed in the kindergarten sinks which will collect data from the handwashing activities, but it will not provide any feedback or screen activity. A “how-to” teaching session (video-based training) will be held in each kindergarten in the middle of the baseline phase for all children to learn the same hand hygiene information. The second phase will be the treatment and will last for three weeks. The third phase will be the post-intervention, and it will also last for three weeks. After this phase, the systems will be de-installed from all the kindergarten sinks. In Finland, there will be a twelve-month follow-up after the intervention.

The control group will have no screen display next to the sink throughout the study. The intervention A (instruction) group will receive instructions from the screen display next to each sink where handwashing instructions are shown during the handwashing activity but no reward after. The intervention B (reward) and intervention C (reward plus instruction) groups will receive instructions and rewards shown on a screen display right next to the sink during the intervention phase. In these groups, handwashing instruction is shown during the handwashing activity and if handwashing is done correctly (based on time and soap usage), a reward of animal animation is shown on the screen, see Figs 6 and 7. During the post-intervention phase, the intervention C group will remain to have the screen display receiving instructions with no reward. In Finland, sick leave days of the children and kindergarten staff will be tracked (Fig 8).

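### Groups B and C are on the same treatment until the intervention phase ends, but the analysis compares four groups throughout and states no combined B and C contrast for H1 and H4a

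*Protocol article*

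**What the plan says.** **Treatment.** Under Trial design (the text below the Fig 1 caption), the baseline is common to all: "During the baseline phase, all the groups will have no screen activity". In the intervention phase, "the intervention B and C groups will receive handwashing instructions and rewards from the screen display". The two groups part only in the last phase. Implementation says: "During the post-intervention phase, the intervention C group will remain to have the screen display receiving instructions with no reward", while B then has no screen activity.

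**Hypotheses.** H1 (intervention phase) and H4a (after the intervention phase) each name B and C together and place them above A. B and C are distinguished only in hypotheses about the post-intervention phase.

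**Analysis.** Data analyses names one-way ANOVA in general terms. For the sensor data it says: "The data will be analyzed using linear fixed-effect regression model for panel data, and dependent variable soaping time". It continues: "The four groups will be compared in baseline, intervention, and post-intervention phases". The same sentence closes the paragraph on child interviews and observations. The survey and staff data are to be compared across four groups after the intervention phase. According to Data collection, the parent survey is taken in the last week of that phase.

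**Layout.** Sample size plans three kindergartens for four groups and has one cluster cover two intervention groups, without saying which two. The design text (below the Fig 2 caption) and Randomization make each kindergarten one cluster, allocated as a whole.

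**The concern.** Until the post-intervention phase begins, the design holds three conditions: control, instruction, and instruction plus reward. Comparing four groups in that period sets B against C although nothing in their treatment differs. Any gap reflects kindergarten or sampling variation.

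Three things are at stake:

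- **Precision.** If reward is judged by B versus A and C versus A separately, each comparison uses only part of the reward data.
- **Number of tests.** By pairs, H1 needs five comparisons (A, B and C each with control; B and C each with A). With B and C combined it needs three.
- **Interpretation.** The parent survey is collected only while B and C are treated alike, so a B-C difference in it cannot be a treatment effect.

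**Working it through.** **1. The plan's own figure.** Inputs from Sample size: "0,35 (large effect size) and power level of 0.8"; "2 predictors and a probability level of 0.05 leads to n = 31"; "With the ICC from the pre-study of 0.062, and estimated cluster size (size of each kindergarten) of 40 children".

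- Overall F test with 2 predictors and noncentrality 0.35 × n: power is 0.789 at n = 30 and 0.804 at n = 31, so n = 31 reproduces.
- Design effect: 1 + 39 × 0.062 = 3.418. Then 31 × 3.418 = 105.96, so 106 reproduces. The printed multiplier 4.418 is a slip, since 31 × 4.418 = 136.96.

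**2. Variance of a group mean, in SD units.** V(m) = [1 + (m − 1) × ICC] / m for m children in one kindergarten.

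- Whole kindergarten: V(40) = 3.418/40 = 0.08545.
- Half kindergarten: V(20) = (1 + 19 × 0.062)/20 = 0.1089.

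The 20/20 split of a shared kindergarten is my assumption, as are equal SDs and the use of ICC 0.062 for every outcome.

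**3. Each group in its own kindergarten of 40.**

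- A (or control) versus B alone: √(2 × 0.08545) = 0.413.
- A (or control) versus the mean of B and C: √(1.5 × 0.08545) = 0.358.
- Ratio: √(1.5/2) = 0.866 at any ICC, so the SE is 13.4% lower. By normal approximation (two-sided 0.05), a contrast with 80% power rises to about 90%.

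**4. B and C share one kindergarten; A and control have their own.**

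- A (or control) versus B alone: √(0.08545 + 0.1089) = 0.441.
- A (or control) versus B and C combined: √(2 × 0.08545) = 0.413.
- Ratio 0.938, so the SE is about 6% lower, and power goes from 80% to about 85%.
- With more observations per kindergarten, as in event-level data, the ratio tends to 1: 0.983 at 200 and 0.996 at 1000.

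**5. A and B share one kindergarten; C and control have their own (A with C is symmetric).** The within-kindergarten variance is 1 − 0.062 = 0.938.

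| Comparison | Variance | SE |
|---|---|---|
| A vs B (within the kindergarten) | 2 × 0.938/20 = 0.0938 | 0.306 |
| A vs C | 0.08545 + 0.1089 = 0.1944 | 0.441 |
| A vs mean of B and C, equal weights | 2 × 0.25 × 0.062 + 0.938 × (1/20 + 0.25/20 + 0.25/40) = 0.0955 | 0.309 |
| A vs B and C weighted by size (1/3, 2/3) | 2 × (4/9) × 0.062 + 0.938 × (1/20 + (1/9)/20 + (4/9)/40) = 0.1176 | 0.343 |
| Control vs B | 0.08545 + 0.1089 = 0.1944 | 0.441 |
| Control vs C | 2 × 0.08545 = 0.1709 | 0.413 |
| Control vs mean of B and C | 0.08545 + 0.25 × (0.08545 + 0.1089) = 0.1340 | 0.366 |

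Against A, combining gains nothing over the within-kindergarten comparison with B. Against control it still helps.

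**6. Omnibus test.** A large-sample (chi-square) test at 0.05 with 80% power on 2 degrees of freedom (three conditions) has about 74% on 3 (four groups), if B and C truly do not differ.

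**7. Can the B-C gap in the intervention phase check the standard errors?**

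- Separate kindergartens: true SE 0.413 against an unclustered SE of √(2/40) = 0.224. The one available difference exceeds 1.96 unclustered SEs about 29% of the time (10% at an assumed ICC of 0.01, 45% at an assumed 0.15).
- Shared kindergarten: true SE 0.306 against √(2/20) = 0.316. It exceeds the limit about 4% of the time, because the kindergarten effect cancels.

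The check usually misses the problem in the first layout and cannot see it in the second.

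**The case against.** The strongest reply is that the combined comparison already is the hypothesis. H1 and H4a put B and C on one side, and a four-group model can test their mean against A as a single linear contrast, with the same variance as merging equal arms. The article nowhere says that B and C will be tested only separately, and a condensed article commonly leaves exact contrasts to the analysis plan. Four labels are also needed, because the panel model spans all phases and the later hypotheses separate B from C.

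Much of this stands. Keeping four groups in the model is no error, and no hypothesis predicts a B-C difference in the intervention phase. What remains is that the article does state a comparison, of four groups in every phase with one-way ANOVA named, and that comparison does not match H1 and H4a.

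Three stronger readings are tempting and unsupported:

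- **That a chance B-C gap will be reported as an effect.** Nothing in the article says so.
- **That pooling always yields the full 13%, or that half of the reward kindergartens go unused.** Both require B and C in separate, equal kindergartens, and Sample size leaves open which groups share one.
- **That the B-C gap is a free check of the error bars.** Step 7 shows that it is not.

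**Conclusion.** The point holds as a minor, conditional one. B and C are one condition through the end of the intervention phase, H1 and H4a treat them so, and the stated four-group comparison does not. The SE of reward versus A or control falls by up to 13% with one equal kindergarten per group. With B and C in one kindergarten of 40 it falls by about 6%, and by close to nil for event-level sensor data. If A shares with B or C, the gain may be limited to the comparison with control (0.441 or 0.413 down to 0.366).

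The figures rest on the assumptions in step 2. Combining B and C does not touch the graver limits on these hypotheses: one kindergarten or fewer per group under Sample size, and the conflict between that section and the statements that each kindergarten is one cluster allocated as a whole.

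**What to change.** - For H1, H4a and the parent survey, prespecify three conditions: control, instruction, and instruction plus reward with B and C combined. One linear contrast in the four-group model will do, with its weights stated and clustering accounted for.
- Keep B and C separate only for the post-intervention hypotheses. Say that a B-C difference before then will not be interpreted as an effect; it may be shown descriptively, but not as a validation of the standard errors.
- State how many kindergartens each group has and which groups, if any, share one, since the gain depends on it.

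The first two items cost a few sentences in the analysis section and need no new data or design change. The third also means reconciling Sample size with the design text and Randomization, which has to be done in any case.
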